**LIST OF ABBREVIATIONS**

| ADV | Visual Help |
| --- | --- |
| ANSM | French National Agency for the Safety of Medicines |
| ATB | Antibiotic |
| ATC | Anatomical, Therapeutic and Chemical Classification |
| CEREES | Expertise Committee for Research, Studies and Assessments in the field of Health |
| CHU | University Hospital |
| CNIL | Commission Nationale de l'Informatique et des Libertés (French Data Protection Authority) |
| CPAM | Caisse Primaire d'Assurance Maladie |
| DAM | Health Insurance delegate |
| DDJ | Defined Daily Dose |
| ITT | Intention to treat |
| MG | General Practitioner |
| WHO | World Health Organisation |
| ENT | Ear, Nose and Throat |
| RNI | Non-interventional research |
| SNDS | National Health Data System |
| SNIIRAM | National Health Insurance Inter-Scheme Information System |
| WHO | World Health Organization |
|  |  |

1. **RATIONAL OF THE STUDY**

The loss of antibiotic efficacy is a threat to public health [1-4]. The mechanisms behind antibiotic resistance are multiple and complex, but one of the main mechanisms is the high and excessive consumption of antibiotics [5-8]. France is the 4th largest consumer of antibiotics in Europe [9-10]. Between 2011 and 2016, antibiotic consumption in towns and cities rose by 5.6% [10]. In France, as in other countries, the majority of prescriptions are made by GPs. In France, general practitioners account for 70% of these prescriptions. Several studies suggest that non-clinical factors influence these prescriptions, which suggests possible areas for improvement [11,12], particularly in paediatrics [13]. It would therefore seem vital to implement initiatives specifically aimed at GPs.

Numerous experiments have been carried out internationally with a view to changing antibiotic prescribing practices among GPs [14-17]. Simply developing training courses or making information available on the internet does not appear to change practices if these interventions are carried out in isolation [3]. On the other hand, various approaches involving communication training, specific educational interventions based on examples of preconceived ideas, interventions at the point of care, and the use of electronic decision support systems have been shown to have beneficial effects on prescribing [14-27]. Attali et al, in the PAAIR study, showed the importance of working on the preconceived ideas that GPs may have [25]. Giving GPs feedback on their prescribing practices has also been shown to have an impact [14;20;28-30]. Many authors conclude that multifaceted interventions are needed [22]. The case of paediatric prescribing appears to be particularly difficult [31-34]. In a recent study, Gulliford et al. were able to demonstrate that feedback on practices can improve antibiotic prescribing practices in the general population, but this intervention had no impact in paediatrics, or in people over 85 years of age [20].

In France, the Antibioclic website was created in 2011 by a multidisciplinary committee of GPs and infectious diseases specialists from universities and hospitals at the University of Paris Diderot [35,36]. It is a web-based Clinical Decision Support System developed for GPs, which can be accessed directly, freely and at no cost, without the need for identification or registration. It provides advice on prescribing antibiotics for all infectious diseases commonly encountered in primary care, based on current national recommendations. A decision-making algorithm is proposed for 40 infectious diseases encountered in ambulatory care. The originality of the tool lies in its user-friendliness and its ability to propose, in a simple format, a course of action that takes account of patient characteristics: age (child/adult), identification of chronic renal failure, pregnancy or breast-feeding, for example. The Antibioclic committee monitors the literature and adapts the content of the tool as new recommendations are published. Antibioclic has met with growing success since its launch: around 9,500 users log on every day (Google Analytics data^®^ ), making more than 2 million requests a year. In a 2014 cross-sectional survey of 1,344 users, 90% were identified as general practitioners [37].

A number of studies suggest that doctors who use Antibioclic have different antibiotic prescribing practices to those who do not. In 2016, Heslot C. et al. surveyed 142 general practitioners in Isère to assess the median duration of amoxicillin prescriptions for acute community-acquired pneumonia. In this survey, 79% of respondents stated that they used Antibioclic to obtain information on antibiotic therapy, whereas only 58% consulted national recommendations, 52% consulted specialist medical journals and 34% consulted the website of the Société de pathologie infectieuse de langue française (SPILF) [38]. Only doctors who reported consulting Antibioclic had a prescription duration in line with the 7-day treatment recommendation [38]. In the Aquitaine region, a prospective study conducted between 25 October 2016 and 3 February 2017 at the Libourne Hospital Centre among 19 GPs found that, out of a total of 136 antibiotic therapy prescriptions, those initiated during a consultation using the Antibioclic tool had a duration more in line with national recommendations, and the choice of molecules used appeared to be more appropriate [39]. One limitation of these studies is that they do not allow conclusions to be drawn about the impact of using the site on practices, or whether using the Antibioclic site is simply a marker for identifying doctors who are more aware (from the outset) of the need to prescribe antibiotics correctly. While some authors suggest that the use of online prescribing aids could help to reduce antibiotic prescribing by doctors [40-41], the Antibioclic website is only used by a minority of professionals.

With a view to optimising prescriptions, our idea for this project is to implement a multi-faceted strategy that can be rolled out nationwide, combining different intervention methods that have demonstrated their impact, and to involve the use of the Antibioclic Clinical Decision Support System. The proposed study will therefore test a multifaceted intervention method based on 1) a visit by a medical representative to doctors' surgeries, with: raising awareness of antimicrobial resistance, work on preconceived ideas as in the PAAIR study, feedback on prescriptions, AND 2) use of the Antibioclic Clinical Decision Support System.

The generalisability of the intervention will be based on collaboration with the Délégués de l'Assurance Maladie (DAM), who are already working on this issue on an operational and regular basis throughout France [42]. The DAMs, who are based throughout the country, make regular visits to GPs and promote good practice [43]. As this method of visiting GPs is original on an international scale, it is vital to demonstrate its impact on practices.

**The aim of the research** is to evaluate the effect of multifaceted interventions on GP prescribing by comparing the volumes of antibiotics dispensed at the end of 12 months of follow-up in a study comparing :

i) an intervention carried out by the Délégués d'Assurance Maladie (health insurance representatives) in general practices, combining a usual visit (with awareness-raising on antibiotic resistance, work on preconceived ideas, feedback on practices) and a demonstration of the use of Antibioclic (arm 1),

ii) an intervention carried out in the same way by Health Insurance delegates but without demonstration of Antibioclic (arm 2),

iii) compared with usual practice (arm 3).

1. **ORIGINALITY AND INNOVATION**

The project proposes an original study based on collaboration between various primary care players: a university team of general practitioners, regional health insurance teams in Pays de la Loire, a university hospital infectiology team, the MedQual centre (Antibiotic Resource Centre for the Pays de la Loire region) and the Antibioclic Clinical Decision Support System team.

The project was co-constructed with the Pays de la Loire health insurance scheme.

The originality of the intervention lies in the approach combining the strengths of tools that already exist and are established, but which act without synergy, despite their strong potential added value: face-to-face interventions by Assurance Maladie delegates in doctors' surgeries, support materials (enabling feedback on practices) built from prescription data collected by Assurance Maladie, and the Antibioclic internet tool to help with prescribing.

The robust design of a randomised study in 3 parallel arms covering the entire population of GPs in an administrative region will enable us to conclude both on the effect of a specific intervention by health insurance delegates in the form of the usual visits implemented by the social security system, and on the specific added value of demonstrating the use of Antibioclic.

The proposed intervention is replicable on a national scale and could serve as a model for the future.

The method chosen for data collection, based on collaboration with health insurance departments and extraction of data from the SNDS, will help to limit missing data.

1. **DESCRIPTION OF EXPECTED BENEFITS**

The aim of the study is to identify the most effective ways of reducing the volume of antibiotics dispensed, with immediate benefits for public health:

. limiting the development of bacterial resistance,

. optimising antibiotic prescriptions (better quality prescriptions),

. lower costs.

The results will provide original information, at the end of a randomised comparative study, on the specific impact of 2 complementary types of intervention:

1. the use of visits by health insurance delegates,

2. demonstration of the use of the Antibioclic site.

Secondary analyses will enable us to better characterise the differentiated impact of the intervention according to prescribers or patient characteristics.

The study will provide an opportunity to raise GPs' awareness of the problem of antibiotic resistance on a large scale, and will raise awareness of :

. more than 800 doctors included in arm 1, who will receive awareness training from the Health Insurance delegate, feedback on their practices, and a demonstration of how to use the Antibioclic website,

. more than 800 doctors included in arm 2, who will benefit from awareness-raising by the Health Insurance Delegate and feedback on their practices.

The medico-economic study will document the potential impact on healthcare expenditure.

One of the ancillary benefits of the study will be to mobilise the partners around a joint project, on a theme that is of daily interest to primary care professionals.

1. **OBJECTIVES AND ASSESSMENT CRITERIA**
   1. ***OBJECTIVE AND MAIN EVALUATION CRITERIA***

***4.1.1. Main objective***

The main objective is to compare the effect on antibiotic dispensing after 12 months of follow-up,

i) an intervention carried out by the Délégués d'Assurance Maladie in general practices, combining a routine visit (raising awareness of antimicrobial resistance, work on preconceived ideas, feedback on practices) and a demonstration of the use of Antibioclic (arm 1),

ii) an intervention carried out in the same way by the Health Insurance delegates, but without Antibioclic being demonstrated (arm 2),

iii) compared to usual practice (arm 3). In the latter arm, the Health Insurance delegates carry out a visit that does NOT involve prescribing antibiotics.

***4.1.2. Primary endpoint***

The primary endpoint will be the overall volume of antibiotics dispensed in defined daily doses (DDD) per participating doctor, at the end of 12 months' follow-up.

Antibiotics used systemically (oral, parenteral, ATC class J01) will be taken into account. Antibiotics used topically by the cutaneous, ocular or auricular route will be excluded.

The DDDs will be calculated by the regional branch of the Assurance Maladie. The method for calculating DDDs will be that used by the World Health Organisation [44,45]. The exhaustiveness of the Assurance Maladie database will limit the risk of measurement bias.

NB: Antibiotic prescriptions are reported to the GP if they follow a prescription bearing the GP's ADELI / RPPS number.

- 1. ***OBJECTIVES AND SECONDARY EVALUATION CRITERIA***
     1. ***secondary objectives***

1/ Analyse the effect on the volumes of antibiotics delivered over time, in each of the 3 arms,

. by comparing the volumes of antibiotics dispensed at the end of 3 months' follow-up,

. by describing monthly changes in the volumes of antibiotics dispensed, over the entire monitoring period (12 months).

The monitoring period for the doctor's prescriptions will begin from the date of the visit by the Health Insurance delegate (T0). (See also Chapter 6.3. Inclusion and follow-up period).

2/ To analyse the specific effect on the volumes of broad-spectrum antibiotics most frequently responsible for antibiotic resistance in primary care (3rd generation cephalosporins, fluoroquinolones, amoxicillin/clavulanic acid) dispensed [8] [9] in each of the 3 arms.

. by comparing the volumes of antibiotics dispensed at the end of 12 months of follow-up,

. by describing monthly changes in the volumes of antibiotics dispensed over the entire monitoring period (12 months).

3/ To analyse the effect on volumes of antibiotics dispensed in two specific patient subgroups: patients aged over 65 (subgroup 1), and children under 6 (subgroup 2), in each of the 3 arms.

. by comparing the volumes of antibiotics dispensed at the end of 12 months of follow-up,

. by describing monthly changes in the volumes of antibiotics dispensed, over the entire monitoring period (12 months).

4/ Analyse the factors associated with the dispensing of antibiotics :

The demographic characteristics (age, sex) of the doctors and their mode of practice (type of commune of practice based on INSEE urban area zoning, "major centres" (codes 111, 112, 120), "small centres" (codes 211, 212, 221, 222), "isolated towns" (code 400), and "other communes" (code 300) [46]), group practice/independent practice, number of procedures/year, number of patients declared as attending physician) will be evaluated as factors potentially associated with the volume of antibiotics dispensed at the end of 12 months of follow-up.

5/ Compare the efficiency of drug dispensing after 12 months of follow-up.

- - 1. ***Secondary evaluation criteria***

The secondary evaluation criteria will be as follows:

1/ Overall volume of antibiotics dispensed at the end of 3 months' follow-up, measured in DDD per participating doctor.

Overall monthly volume of antibiotics dispensed, measured in DDD per participating doctor.

2/ Volume of broad-spectrum antibiotics most frequently responsible for antibiotic resistance in primary care (3rd generation cephalosporins, fluoroquinolones, amoxicillin/clavulanic acid) dispensed, measured in DDD per participating doctor.

3/ Sub-group analyses :

. Volume of antibiotics dispensed to patients over 65 (sub-group 1), measured in DDDs per participating doctor,

. Volume of antibiotics dispensed to children under 6 (sub-group 2), measured in DDD per participating doctor.

4/ Analysis of physician factors associated with the overall dispensing of antibiotics: age, sex, type of practice municipality [46], group practice/independent practice, number of procedures performed during the 12 months of follow-up, total number of patients declared in the attending physician's patient base.

5/ Cost-effectiveness analysis :

Incremental cost-effectiveness ratio comparing the 3 alternatives: i) DAM visit with Antibioclic demonstration, ii) DAM visit without Antibioclic demonstration, iii) usual practice.

1. **STUDY POPULATION**
   1. ***Description of the population***

The study covers the 5 departments of the Pays de la Loire region.

All GPs practising in the region who have seen more than 100 different patients in the year preceding the evaluation will potentially be eligible. The list of eligible GPs in the 5 departments will be established through a partnership with the Assurance Maladie, as in a previous study conducted by our team [47]. A preliminary study will enable us to anticipate the inclusion of more than 2,400 doctors.

- 1. ***Inclusion criteria***

GPs practising in one of the 5 study departments who had seen at least 100 different patients (of any age) in the year preceding the evaluation.

- 1. ***Non-inclusion criteria***

Not included:

. doctors with special practices (acupuncture, allergology, angiology). These doctors will be identified on the basis of health insurance data.

. doctors included in another programme to improve antibiotic prescribing practices run by the Assurance Maladie in the form of a "Plan Personnalisé d'Accompagnement" (CPAM initiative).

. doctors who participated in the design of the study: doctors who took part in the steering groups and working groups, doctors who tested the content of the DAM visit.

1. **DESIGN AND CONDUCT OF THE STUDY**
   1. ***General research methodology***

. This will be a prospective, randomised, controlled, open-label study with 3 parallel arms.

. The study will involve all GPs in the 5 departments of the Pays de la Loire region who meet the inclusion and non-inclusion criteria.

. The statistical unit will be the doctor.

. The source of the data will be the Health Insurance SNDS database for the Pays de la Loire region.

. Randomisation will be based on doctors' surgeries (and not doctors) to limit confounding bias between arms.

. The analysis will be carried out on an intention-to-treat basis.

This is a 'real-life' study.

In particular, it will not be a question of evaluating the effectiveness of the Antibioclic site "*per* protocol".

The challenge will be to assess the effect of the 2 interventions, compared with usual practice, bearing in mind that the Health Insurance Representatives' visit and its potential impact will vary greatly from one doctor to another.

- 1. ***RANDOMISATION; INTERVENTION ARMS and CONTROL ARMS***

**At the end of randomisation, participating doctors will be randomly assigned to one of the following 3 arms:**

**Arm 1: Presentation by the DAM with demonstration of the ANTIBIOCLIC internet tool**

. Raising awareness of antibiotic resistance, highlighting the classes of antibiotics that are sources of resistance,

. A look back at prescribing practices, with a presentation of personal data from the Assurance Maladie,

. Deconstruction of preconceived ideas and strategies for resolving high-risk situations (based on the PAAIR study [23],

. Demonstrating the use of Antibioclic.

The presentation will focus on 2 common pathologies, to deliver key messages: 1) cystitis (message: no place for fluoroquinolones since the SPILF [48] updated its recommendations), 2) bacterial angina (message: amoxicillin alone, very little place for amoxicillin-clavulanic acid in ENT infections). Doctors use Antibioclic by browsing the site themselves. They are guided by the Health Insurance delegate. The intervention includes the installation of the link in favourites, and an incentive to use the site again in the future (see also the description of the DAM intervention in 5.4.).

**Arm 2: DAM intervention without demonstration of the ANTIBIOCLIC internet tool**

. Raising awareness of antibiotic resistance, highlighting the classes of antibiotics that are sources of resistance,

. A look back at prescribing practices, with a presentation of personal data from the Assurance Maladie,

. Deconstructing preconceived ideas and strategies for resolving high-risk situations,

. Presentation and distribution of paper memos on 2 common pathologies, and delivery of key messages: 1) cystitis (message: no place for fluoroquinolones since the SPILF [48] updated its recommendations), 2) bacterial angina (message: amoxicillin alone, very little place for amoxicillin-clavulanic acid in ENT infections).

**Arm 3. Usual practice (without intervention relating to antibiotic prescribing)**

. Presentation of a different theme (not relating to antibiotic prescribing or antibiotic resistance) during the Health Insurance representative's visit to the doctor.

- 1. ***Creation of the necessary support materials***

The various partners in the project will work together to create the materials required for the 2 intervention arms: the Department of General Medicine at the University of Nantes, the Pays de la Loire Health Insurance Scheme - including representatives of the health insurance delegates - and the antibiotic referral agents at Nantes University Hospital.

The project includes a number of preparatory meetings to develop the materials needed for the DAMs' work. These materials will be essential for standardising the visit and the messages delivered in the two arms presenting the antibiotics theme.

- The work of the Health Insurance Representatives will be based on a digital visual aid, a slide show on an I-Pad-type tablet usually used by the DAMs when visiting doctors.

The digital visual aid will successively review epidemiological data on antibiotic resistance and 3 major factors in bacterial resistance (wrong indication, wrong duration, wrong molecule).

This will be followed by a discussion of practical solutions to these 3 causes of overconsumption: presentation of Antibioclic (in arm 1), or distribution of memo cards (in arm 2),

Lastly, the support will lead to a discussion of preconceived ideas about antibiotics, and will propose strategies to help patients avoid prescribing, based on the PAAIR study [25].

With a view to training the DAMs, the study includes the drafting of a detailed sales pitch corresponding to the elements included in the digital visual aid. Exploring in greater depth all the information contained in the digital visual aid should enable DAMs to feel at ease with the subject, to be aware of the specific issues involved in prescribing antibiotics in primary care, and to be able to answer any questions from the doctors visited.

- The project involves the production of fact sheets based on the CNAM fact sheets on upper respiratory infections and urinary tract infections:

. Upper respiratory infections :

The plan is to simplify and prioritise the information in the table of treatments on the initial CNAM form: amoxicillin will be given priority over other molecules, a single 2^e^ generation cephalosporin will be proposed in cases of allergy to penicillins (the one with the shortest duration of treatment), and amoxicillin-clavulanic acid will be relegated to exceptional use.

. Urinary tract infections: acute cystitis in non-pregnant women and men and acute cystitis in pregnant women.

The project involves updating the CNAM memo sheet with the latest SPILF recommendations from 2017 [48] instead of the 2015 HAS recommendations.

- 1. ***F*** ***ormation DAM***

Training for DAMs will be developed in collaboration with the various partners in the project: the Department of General Medicine at the University of Nantes, the Pays de la Loire health insurance scheme, involving representatives of the health insurance delegates, and the antibiotic referral agents at Nantes University Hospital.

The project is planning several preparatory meetings to set up training for the DAMs. The training of the DAMs will be essential in order to standardise the visit and the messages delivered in the two arms presenting the antibiotic theme.

- - 1. ***Creation of role plays for training DAMs***

The project involves the creation of role-playing games to enable the DAMs to take ownership of the discussion sessions with GPs. This type of role-playing session is customary in the training of DAMs prior to their work with GPs.

One of the role-plays will be built around a profile of a doctor with a higher rate of prescribing amoxicillin and clavulanic acid than the departmental average.

The second role-play will be built around a profile of a doctor with a higher rate of fluoroquinolone prescribing than the departmental average.

- - 1. ***Course of training for DAMs***

DAM training must include :

- presentation of the study protocol, emphasising the need to ensure random allocation of doctors to the 3 arms.
- presentation of the digital visual aid on the I-Pad tablet, which will be used by the DAMs during visits by doctors.

The presentation will review the epidemiological data on antibiotic resistance and the 3 major factors in bacterial resistance (wrong indication, wrong duration, wrong molecule).

The presentation will describe the practical solutions proposed in response to these 3 causes of overconsumption: presentation of antibioclic (arm 1) or distribution of memo cards (arm 2), discussion of preconceived ideas about antibiotics, and presentation of strategies to help avoid prescribing resulting from the PAAIR study [25].

- the presentation of detailed arguments, so that the DAMs are at ease with the subject, are aware of the specific problems of antibiotic prescribing in primary care, and can answer any questions from the doctors visited.
- presentation of CNAM memo sheets on upper respiratory infections and urinary tract infections. (
  1. ***Inclusions and follow-up period***

The period during which the doctor's prescriptions will be monitored will begin on the date of the DAM's visit (T0). For doctors in arms 1 and 2, the DAM's visit will be staggered over approximately 3 months, corresponding to the time usually required for DAMs to visit all the doctors in their intervention zone. For doctors in arm 3, the date of the DAM's visit will be noted even though the DAM will not be making a specific intervention relating to the prescription of antibiotics (presentation of a different topic during the visit by the Health Insurance Representative to the doctor). Monitoring will last 12 months from the date of the DAM's visit.

- 1. ***Study timetable***

M - 3: Health Insurance Representatives will be trained 3 months before the start of the first visits to doctors.

**T0:** Start of DAM visits to GPs.

M3: End of the cycle of visits made by the DAMs to GPs as part of the study.

Monitoring period*:* The doctor's prescriptions will be monitored from the date of the DAM's visit to the GP (T0). However, the DAMs' visits will be staggered over approximately 3 months, corresponding to the time usually required for the DAMs to visit all the doctors in their area of intervention. For doctors in arm 3, the date of the DAM's visit will be noted even though the DAM will not be making a specific intervention relating to the prescription of antibiotics (presentation of a different topic during the visit by the Health Insurance Representative to the doctor).

*NB: we are anticipating a potential additional 15-day period, beyond the 3-month period initially planned, in order to anticipate some postponements of appointments when doctors are on holiday.*

Monitoring will last 12 months from the date of the DAM's visit.

M15 (+ 15 days): End of the monitoring period corresponding to the last doctors visited.

1. **DATA MANAGEMENT AND STATISTICS**
   1. ***extraction of study data***
      1. ***DATA COLLECTION, PROCESSING AND CIRCULATION***

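### Arm 1 versus arm 2 compares the Antibioclic demonstration with paper memo cards, not with the same visit without the demonstration, so it cannot give the added value the protocol claims

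*Protocol*

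**What the plan says.** The protocol describes arm 2 in two ways.

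**As a visit with one element removed.** The aim, at the end of the rationale, calls arm 2 "an intervention carried out in the same way by Health Insurance delegates but without demonstration of Antibioclic (arm 2"). The main objective (4.1.1) repeats this: "an intervention carried out in the same way by the Health Insurance delegates, but without Antibioclic being demonstrated (arm 2"). Both list the visit's content as awareness-raising, preconceived ideas and feedback; neither mentions cards. The section on expected benefits describes arm 2 as awareness and feedback only, and promises results on the specific impact of the visits and of the demonstration as two kinds of intervention. The section on originality says the three-arm design will permit a conclusion on the "specific added value of demonstrating the use of Antibioclic".

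**As a visit with one element replaced.** The arm 1 description lists awareness, feedback, preconceived ideas and then "Demonstrating the use of Antibioclic". The arm 2 description lists the same first three elements and then "Presentation and distribution of paper memos on 2 common pathologies, and delivery of key messages". The section on support materials presents the two tools as alternatives, "presentation of Antibioclic (in arm 1), or distribution of memo cards (in arm 2"), and the section on the delegates' training course does the same: "presentation of antibioclic (arm 1) or distribution of memo cards (arm 2").

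Under the planned statistical methods, arm 1 is tested against arm 3 first and, if that test is significant, arm 1 against arm 2.

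**The concern.** The second confirmatory comparison is the only one placed to answer what the demonstration contributes beyond the delegate's visit. If arm 2 carries its own tool, the comparison answers a different question.

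The protocol does not treat the cards as inert. The support-materials section puts them beside Antibioclic as a practical answer to overconsumption. It also plans to rewrite the existing national sheets so that some molecules gain priority and others lose it, and the medico-economic section counts the rewriting time as a resource.

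What is at stake is the conclusion drawn from a pre-specified test, above all when it is not significant. The hierarchy reaches that test only after arm 1 has beaten usual practice. A null second result could then be read as the visit having done all the work and the demonstration nothing, which the data could not establish. The arm 1 versus arm 2 cost-effectiveness ratio raises the same difficulty, because the secondary evaluation criteria label arm 2 only as the visit without the demonstration.

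**Working it through.** The protocol gives no figure for this point, so the check sets the arm contents side by side and asks what each contrast can identify.

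**Contents of each arm, from the arm descriptions**

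| Element | Arm 1 | Arm 2 | Arm 3 |
|---|---|---|---|
| Awareness of resistance | yes | yes | no |
| Feedback on own prescribing | yes | yes | no |
| Preconceived ideas | yes | yes | no |
| Key messages on cystitis and bacterial angina | yes | yes | no |
| Antibioclic demonstration | yes | no | no |
| Paper memo cards | not listed | yes | no |

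Two places mention the sheets without naming an arm: the part of the support-materials section on producing them, and the last item of the delegates' training course. Neither assigns cards to arm 1, and both sections elsewhere state the either/or allocation.

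**What the contrasts estimate.** For mean 12-month volume per doctor, let

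- U = the mean under usual practice,
- V = the reduction from the common visit with neither tool,
- A = the further reduction when the demonstration is added to that visit,
- m = the further reduction when the cards are added to that visit.

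Then:

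- arm 1 mean = U − V − A
- arm 2 mean = U − V − m
- arm 3 mean = U

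The differences are:

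- arm 3 − arm 1 = V + A (first test)
- arm 2 − arm 1 = A − m (second test)
- arm 3 − arm 2 = V + m (not in the hierarchy)

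No arm receives both tools, so this needs no assumption about how A and m would combine.

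**Consequence.** There are three arm means and four unknowns. V, A and m cannot be separated, and no combination of the three contrasts isolates A. The added value claimed is A; the second test delivers A − m. As a share of A, for A > 0, it is 1 − m/A:

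- m = 0: the whole of A
- m between 0 and A: part of A
- m = A: zero, although the demonstration works
- m > A: the contrast favours arm 2

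The documents give no value or range for m, so the position on this scale cannot be fixed.

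**The case against.** The strongest reply is that arm 2 is a deliberate, content-matched comparator. Both arms deliver the same two key messages, and the tools fill one slot in the visit. An arm 2 with no aid would mix the effect of the web tool with those of having an aid and of contact time. The short label in the objective also heads the arm 2 description, which lists the cards directly beneath it, so nothing is concealed. In a real-life study, added value could mean what Antibioclic adds to a delegate visit that uses paper aids.

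Much of this stands. One component is substituted, an active comparator is a legitimate choice, and randomisation protects the comparison of the two packages. A reader might infer that the arm 1 versus arm 2 contrast is biased or invalid. The documents do not support that: it falls short only when read as the effect over a visit with no tool.

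The last part does not stand. The protocol says the visits take the form of usual ones and that the cards adapt existing national sheets, but nowhere that paper cards belong to a usual visit. If they did, arm 1 would have lost a usual element and the two visits would still not be carried out in the same way. The objective and the conclusion promised in the originality section do not declare an active comparator.

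**Conclusion.** The concern holds as a mismatch between the comparison delivered and the conclusion claimed. Arm 1 versus arm 2 is a sound randomised comparison of the demonstration with memo cards on top of a common visit. It does not give the demonstration's added value over that visit, and a null result would not show that this value is nil.

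The discrepancy equals the effect of the cards, which is unknown from the documents. The conclusion rests on the arm descriptions being the operative ones; if doctors in arm 1 are also meant to receive cards, the protocol does not say so.

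Two stronger inferences should be resisted. The first test, arm 1 versus arm 3, is unaffected, since it compares a defined package with usual practice. And nothing in the protocol says that a null second test will be reported as proof of no benefit; the risk is that the present wording invites that reading.

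**What to change.** Reword so that the stated question matches the arms:

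- In the aim, the main objective and the expected benefits, state that the arm 2 visit includes presenting and handing out the paper memo cards.
- Describe the second hierarchical comparison as *Antibioclic demonstration versus paper memo cards, both added to the same delegate visit*, and state the planned conclusion in those terms.
- Remove the added-value claim from the originality section, or qualify it as value relative to memo cards; treat the promise of a specific impact under expected benefits in the same way.
- Label the arm 1 versus arm 2 cost-effectiveness comparison likewise, and say which arm is meant by the standard delegate visit in the willingness-to-pay analysis.

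This changes no arm, test or sample size. The price is a narrower claim: the trial can say whether the demonstration does better than cards, not what it adds to a visit with neither.

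Handing the cards to arm 1 as well is not recommended. It would change the package in the first confirmatory test and in the cost-effectiveness analysis. It would also estimate the demonstration's effect on top of cards carrying the same messages, which is again not its effect on top of the visit alone.
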